#### REM sleep.

REM sleep is assessed at home for four consecutive nights using a portable PSG device, the Dreem 3 Ambulatory Electroencephalography (EEG) system (Dreem™, France, Paris). Night 1 serves as an adaptation night, Night 2 serves as a baseline night, and nights 3 and 4 serve as the experimental nights. The Dreem 3 device is a wireless headband worn during sleep. Two main types of sensors in the device are used to record sleep-related physiological data: (1) five dry EEG electrodes (F7, F8, O1, O2, and Fp2) yielding five derivations (F7-O1, F8-O2, F8-F7, F8-O1, and F7-O2) recording cortical activity in the brain, (2) a 3D accelerometer records movement, respiratory rate/trace, and head position. Signal acquisition and the automatic algorithm for sleep staging used by the device have been shown to be comparable to standard PSG scored by expert sleep technicians [35]. We will utilize the automatic scoring algorithm to identify sleep stages. In those cases where signal quality is not sufficient for automated scoring (signal quality is an output of the algorithm), two trained technicians will manually score the PSG. REM sleep data recorded from experimental nights 3 and 4 will be used to test our hypotheses.

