**Figure 3. F3:**
[figure not shown]
Pre- and post-treatment testing protocol. Pre- and post-treatment testing protocol involving 4 nights of at-home PSG and 3 mornings of in-lab FPS testing. The first night serves as an adaptation night and the second night serves as a measure of baseline sleep. The following three mornings, participants complete the fear and safety acquisition phase, extinction learning and safety recall phase, and extinction recall phase of the FPS protocol, respectively (See Figure 4). *FPS fear-potentiated startle, PSG polysomnography.*

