#### Fear inhibition

After baseline night (night 2), fear inhibition is assessed using the fear-potentiated startle (FPS) task over three consecutive mornings on days 3–5 (see Figure 3). The FPS task is a well-validated paradigm that relies on the acoustic startle reflex to measure conditioned fear. The task is sensitive to PTSD symptoms as well as manipulations of sleep [6, 24] Testing sessions occur 2 hours following participants’ habitual wake time, as fear extinction is strongest in the morning [36]. To take into account effects of state anxiety and sleepiness on task responses, participants complete the Karolinksa Sleepiness Scale (KSS) [37] immediately before each testing session, and the State-Trait Anxiety Inventory (STAI) [38] immediately before and after each session. For all sessions, participants are seated in a sound-attenuated room and visual cues are presented via an LCD monitor. Two Ag/AgCl electrodes are positioned on the left orbicularis oculi muscle (approximately 1cm below the pupil and 1cm below the lateral canthus), and a ground electrode is placed on the left mastoid. These sensors are fitted to measure electromyography (EMG) of the blink reflex to startling tones. EMG data sampling rate is 1 KHz. Data are amplified from 0.5 mV electrode input to 2500 mV signal output, band-pass filtered (100–1000 Hz), rectified, and smoothed with a 5-point rolling average. These EMG data serve as operational measures of conditioned fear, safety learning, safety recall, extinction learning, and extinction recall. Fear inhibition is operationalized as safety recall and extinction recall. The FPS task involves three phases (see Figure 4).

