#### Morning 1: fear/safety acquisition.

In the first session, participants acquire conditioned fear to a visual cue (conditioned stimuli, CS+). A mildly aversive 275-280 PSI puff of air to the larynx serves as the unconditioned stimulus (US). Testing begins with a 2-minute acclimation period followed by 3 types of trials in pseudo-randomized order across 8 blocks: 2 conditioned stimulus (CS) trials and 1 no-stimulus trial. In each CS trial, participants are presented with 1 of 2 possible shapes for 6 seconds. One shape (e.g. a blue circle) is paired with the air puff 75% of the time and serves as the fear-conditioned stimulus (CS+). The other shape (e.g. yellow circle) is never paired with the aversive puff and serves as the safety signal (CS−). Participants are not explicitly informed of the predictive quality of these cues but are asked to report air puff expectancy (“yes,” “no,” or “unsure”) for each trial to track their CS+/CS− contingency learning. Between 4 and 5 seconds after the onset of each shape, a startle probe (108-dB 40 milliseconds burst of white noise) is delivered binaurally via headphones to assess fear conditioning. In the no-stimulus trial, the startle probe is presented in the absence of any visual cue (i.e. noise alone [NA)] to get a measure of baseline startle. Fear-potentiated startle is operationalized as eyeblink magnitude in response to the startle probe when presented in the presence vs. absence of the CS+ (i.e. CS+ trials—NA trials). Fear Conditioning will be assessed as the degree of startle potentiation (vs. NA trials) in the presence of the CS+, relative to startle potentiation in the presence of the CS− in the last block of trials. Safety Signal Learning will be assessed by calculating changes in startle amplitude to the CS− from the first block (when participants typically startle to all stimuli), to the last block (when they have learned the CS− predicts safety) [19]. To minimize practice effects, different visual cues will be used at each time point (pre- and post-treatment) and order will be counterbalanced.

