### Data analysis plan

All analyses will be conducted on an intention-to-treat basis. To address missing data, multiple imputation [75] will be used for regression-based analyses, and full information maximum likelihood [76] will be used for mediation analyses. Independent samples t-tests will first be used to examine potential differences in demographic variables between the treatment and control groups (e.g. age, sex, and ISI), whilst controlling for family-wise error rates.

*Aim 1*

Hypothesis 1: REM sleep predicts fear inhibition performance the next day. Two simple linear regression analyses will be conducted to assess how well REM fragmentation (i.e. low values on the REM Sleep latent variable) the night before predicts extinction and safety recall the following day. Baseline REM fragmentation on night 3 will be used as a predictor for level of safety signal recall the next day. Similarly, baseline REM fragmentation on night 4 will be used as a predictor for level of extinction recall the next day. The analyses will include parameters for sex and serum estradiol as covariates. In separate exploratory analyses, average REM sleep over the prior 3 or 4 nights, respectively, and each of the three REM variables will also be examined as explanatory variables. Finally, we will run sensitivity analyses utilizing baseline ISI scores as the explanatory variable to further examine the overall hypothesis that REM sleep abnormalities in Insomnia Disorder, rather than insomnia severity more generally, affect fear extinction and safety signals.

*Aim 2*

Hypothesis 2(a): Treating insomnia enhances fear inhibition. A linear mixed model will be used to examine the effect of treatment exposure (i.e. condition) on fear inhibition (i.e. extinction recall and safety recall). The model will include parameters for treatment condition, baseline fear inhibition, sex, and serum estradiol as a covariate.

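### The H1 model leaves out the session-1 startle response, which is part of the recall score and precedes the REM night used to predict it, so acquired fear is an unadjusted potential confounder

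*Protocol article*

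**What the plan says.** The section on REM sleep gives each night a role: "Night 1 serves as an adaptation night, Night 2 serves as a baseline night, and nights 3 and 4 serve as the experimental nights". It then limits hypothesis testing: "REM sleep data recorded from experimental nights 3 and 4 will be used to test our hypotheses".

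The section on fear inhibition fixes the order of events: "After baseline night (night 2), fear inhibition is assessed using the fear-potentiated startle (FPS) task over three consecutive mornings". Morning 1 is acquisition with the air puff. Morning 2 is extinction learning and the safety recall test. Morning 3 is the extinction recall test.

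The data analysis plan for H1 pairs nights with outcomes: "Baseline REM fragmentation on night 3 will be used as a predictor for level of safety signal recall the next day", and "baseline REM fragmentation on night 4 will be used as a predictor for level of extinction recall the next day". Baseline here means the pretreatment time point, not night 2. The named covariates are sex and serum estradiol. Night 2 enters only an exploratory predictor, "average REM sleep over the prior 3 or 4 nights, respectively".

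The outcomes are change scores anchored in session 1. Extinction recall runs from the maximal acquisition CS+ response to the first-block average in session 3. Safety recall runs from the last CS- block of session 1 to the first CS- block of session 2.

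**The concern.** Acquisition falls between night 2 and night 3, so the REM measure that predicts extinction recall is taken after the session that supplies one of the two terms in the extinction recall score. A participant who conditions strongly has a larger acquisition term. If strong conditioning also disturbs sleep over the next two nights, acquired fear drives both predictor and outcome, and nothing in the H1 model removes it. The same structure applies to safety recall through the last session-1 CS- block.

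Aim 1 is worded as the contribution of REM sleep to fear inhibition, and the Limitations section describes the trial as essentially a mechanism study. An H1 coefficient that mixes a REM effect with an acquired-fear effect does not answer that aim cleanly. A true relationship could be missed. The exploratory average does not help, because it pools night 2 with the adaptation night and with nights that follow conditioning.

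**Working it through.** **1. The plan's own figure.** Inputs from Power considerations: r = 0.40, alpha 0.05, n = 62, power 0.90. By Fisher z, two-sided, n = ((1.960 + 1.282) / atanh(0.40))² + 3 = (3.242 / 0.4236)² + 3 = 61.54, rounded up to 62. The figure reproduces. Power with k covariates is Φ(atanh(r) × √(n - 3 - k) - 1.960). With k = 0 this is Φ(0.4236 × 7.681 - 1.960) = 0.902.

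**2. Size of the distortion, under assumptions.** Let a be the correlation of acquired fear with night-4 REM quality and b the direct standardised contribution of acquired fear to the recall score. Neither is in the documents. Take 0.40 as the direct standardised effect of REM. The correlation seen without adjustment is then 0.40 + a × b.

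| a | b | a × b | correlation seen | power, n = 62, k = 0 |
|---|---|---|---|---|
| -0.1 | 0.4 | -0.04 | 0.36 | Φ(0.3769 × 7.681 - 1.960) = 0.83 |
| -0.3 | 0.8 | -0.24 | 0.16 | Φ(0.1614 × 7.681 - 1.960) = 0.24 |

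The induced term is negative. H1 predicts a positive relation between REM quality and recall, so under these signs the bias works against H1.

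**3. Which adjustment removes it.** A simulation had no REM effect on recall, n = 62, b = 0.5, |a| = 0.2 to 0.6, a night-2 to night-4 REM link of 0.3 or 0.6, and 3,000 runs per setting. Two-sided rejection rates at nominal 0.05 were:

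- night-4 REM alone: 0.12 to 0.67
- night-4 REM adjusted for night-2 REM: 0.12 to 0.86
- night-4 REM adjusted for acquired fear: 0.05 to 0.06
- night-2 REM alone: 0.04 to 0.06

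These rates are two-sided. With the signs in step 2 the rejections would fall in the direction opposite to H1. Adjusting for night 2 does not help; adjusting for acquired fear does.

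**4. Night 2 is not a clean test.** The simulation let night-2 REM have no influence on acquisition. If it correlates 0.3 with acquired fear (assumed) and b = 0.5, the induced correlation with recall is 0.3 × 0.5 = 0.15. The two-sided rejection rate at n = 62 is then 0.21, with no REM effect on recall beyond acquisition.

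**5. Cost and gain of the covariate.** At a partial r of 0.40 and n = 62, power is Φ(0.4236 × √57 - 1.960) = 0.892 with the two planned covariates and Φ(0.4236 × √56 - 1.960) = 0.887 with one more. That treats the covariate as explaining nothing. In the step-2 settings it explains outcome variance:

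- Residual variance is 1 - (0.16 + b² + 0.8ab), which is 0.712 and 0.392 in the two rows.
- The partial correlation is √(0.16(1 - a²) / (0.16(1 - a²) + residual)), which is √(0.1584 / 0.8704) = 0.427 and √(0.1456 / 0.5376) = 0.520.
- Power with k = 1 is 0.93 and 0.99, against 0.83 and 0.24 unadjusted.

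These gains are upper limits, because they assume that the startle measure captures acquired fear without error.

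**The case against.** The strongest reply is that nights 3 and 4 are the right nights. H1 concerns sleep between learning and next-day recall: night 3 lies between safety learning and safety recall, night 4 between extinction and extinction recall. Night 2 precedes all learning. This stands, and choosing nights 3 and 4 is not an error.

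Several stronger readings that a reader might infer also fail:

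- **That the association could run from recall to REM.** Each REM night precedes the recall it predicts. The issue is confounding by acquired fear.
- **That the two explanations cannot be separated.** Night-2 REM and session-1 startle are both recorded, so the data allow it; the stated H1 model does not do it.
- **That H1 would be falsely confirmed.** With the signs assumed above the artefact is opposite to H1.
- **That a night-2 association would settle the direction.** Night-2 REM may act through acquisition, or reflect stable traits that affect both REM and startle.
- **That Aim 2 as a whole is affected.** H2a uses no REM data and compares randomised groups. H2b uses pre-to-post changes, in which stable differences in conditionability largely cancel.

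It is also fair that nothing in the documents shows that a mild air puff alters REM. Stronger conditioning may raise both terms of the extinction recall score, so even the net sign of b is uncertain. The planning value of 0.40 was based on observed correlations in the team's own studies, which may already contain some of this bias.

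A journal article may leave sensitivity analyses to a fuller plan. Here, however, the article names the H1 covariates, and the anchoring session-1 response is not among them. If the fuller plan already contains this adjustment, the point is met.

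**Conclusion.** The point holds for H1 as a missing adjustment. The order of sessions, the anchoring of both recall scores in session 1 and the two-covariate H1 model are all in the text. Together they leave acquired fear as an unadjusted potential common cause of predictor and outcome. Whether it acts, and how strongly, cannot be learned from the documents. Over the assumed range the loss runs from slight (0.36 seen for 0.40, power 0.83) to serious (0.16 seen, power 0.24), and it attenuates the association. The remedy is cheap under either extreme, so it is worth making before results are seen. Confidence is medium, because the magnitude rests entirely on assumed correlations.

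**What to change.** Keep REM on nights 3 and 4 as the primary predictors. In H1, add the session-1 response that anchors each score: maximal acquisition CS+ startle for extinction recall, and last-block CS- startle for safety recall. Do this in the main model or in a prespecified sensitivity model. With the anchor in the model, the REM coefficient equals, apart from sign, the one obtained by modelling the recall-phase response given session 1, so the shared term no longer drives it.

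Replace the pooled 3- or 4-night exploratory average with night-2 REM alone as a supportive predictor. State in advance that an association on night 2 will not be read as proof of an effect on recall.

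Leave H2a unchanged. In H2b, treatment may itself change the post-treatment session-1 response, so adjustment there should be a sensitivity analysis only.

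The cost is plan wording, one degree of freedom per H1 model (0.892 to 0.887 at a partial r of 0.40, n = 62) and one extra run. No new data are needed.

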#### Fear inhibition

After baseline night (night 2), fear inhibition is assessed using the fear-potentiated startle (FPS) task over three consecutive mornings on days 3–5 (see Figure 3). The FPS task is a well-validated paradigm that relies on the acoustic startle reflex to measure conditioned fear. The task is sensitive to PTSD symptoms as well as manipulations of sleep [6, 24] Testing sessions occur 2 hours following participants’ habitual wake time, as fear extinction is strongest in the morning [36]. To take into account effects of state anxiety and sleepiness on task responses, participants complete the Karolinksa Sleepiness Scale (KSS) [37] immediately before each testing session, and the State-Trait Anxiety Inventory (STAI) [38] immediately before and after each session. For all sessions, participants are seated in a sound-attenuated room and visual cues are presented via an LCD monitor. Two Ag/AgCl electrodes are positioned on the left orbicularis oculi muscle (approximately 1cm below the pupil and 1cm below the lateral canthus), and a ground electrode is placed on the left mastoid. These sensors are fitted to measure electromyography (EMG) of the blink reflex to startling tones. EMG data sampling rate is 1 KHz. Data are amplified from 0.5 mV electrode input to 2500 mV signal output, band-pass filtered (100–1000 Hz), rectified, and smoothed with a 5-point rolling average. These EMG data serve as operational measures of conditioned fear, safety learning, safety recall, extinction learning, and extinction recall. Fear inhibition is operationalized as safety recall and extinction recall. The FPS task involves three phases (see Figure 4).

**Figure 4. F4:**
[figure not shown]
FPS protocol. FPS protocol used in the current study involves 3 consecutive days of testing. Day 1 (Fear/Safety Acquisition) includes 8 presentations of the CS+ (e.g. blue circle) paired with an air puff to the larynx 75% of the time, 8 presentations of the CS- (e.g. yellow circle) never paired with the air puff, and 12 NA trials where the 108-dB startle probe is delivered in the absence of any visual cue. Day 2 (Extinction Learning) includes 16 CS+ and 16 CS- presentations, and 20 NA trials. However, no air puffs are delivered in this session. Day 3 (extinction recall) includes 8 CS+ and 8 CS- presentations, and 12 NA trials. Again, no air puffs are delivered in this session. *CS+ conditioned fear cue, CS- conditioned safety cue.*

#### Morning 1: fear/safety acquisition.

In the first session, participants acquire conditioned fear to a visual cue (conditioned stimuli, CS+). A mildly aversive 275-280 PSI puff of air to the larynx serves as the unconditioned stimulus (US). Testing begins with a 2-minute acclimation period followed by 3 types of trials in pseudo-randomized order across 8 blocks: 2 conditioned stimulus (CS) trials and 1 no-stimulus trial. In each CS trial, participants are presented with 1 of 2 possible shapes for 6 seconds. One shape (e.g. a blue circle) is paired with the air puff 75% of the time and serves as the fear-conditioned stimulus (CS+). The other shape (e.g. yellow circle) is never paired with the aversive puff and serves as the safety signal (CS−). Participants are not explicitly informed of the predictive quality of these cues but are asked to report air puff expectancy (“yes,” “no,” or “unsure”) for each trial to track their CS+/CS− contingency learning. Between 4 and 5 seconds after the onset of each shape, a startle probe (108-dB 40 milliseconds burst of white noise) is delivered binaurally via headphones to assess fear conditioning. In the no-stimulus trial, the startle probe is presented in the absence of any visual cue (i.e. noise alone [NA)] to get a measure of baseline startle. Fear-potentiated startle is operationalized as eyeblink magnitude in response to the startle probe when presented in the presence vs. absence of the CS+ (i.e. CS+ trials—NA trials). Fear Conditioning will be assessed as the degree of startle potentiation (vs. NA trials) in the presence of the CS+, relative to startle potentiation in the presence of the CS− in the last block of trials. Safety Signal Learning will be assessed by calculating changes in startle amplitude to the CS− from the first block (when participants typically startle to all stimuli), to the last block (when they have learned the CS− predicts safety) [19]. To minimize practice effects, different visual cues will be used at each time point (pre- and post-treatment) and order will be counterbalanced.

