### Randomization

Following screening assessments, participants are randomly assigned to either an active treatment or waitlist control condition, with a 1:1 allocation as per a computer-generated randomization schedule, stratified by sex (male vs. female), using permuted blocks. To ensure concealment, block size will not be disclosed. Allocation sequence is stored in a spreadsheet created by a researcher not actively involved in enrollment and assignment of participants to conditions. The sequence is concealed by making the cells opaque until a participant is screened, deemed eligible, and ready to be assigned to a condition. Then, the next cell in the sequence is revealed. To help reduce predictability of condition orders for study staff, men and women have separate randomization orders.

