#### Morning 3: extinction recall.

The third session is identical to session 2 and serves as a test of extinction retention. Consistent with prior research using this paradigm [24, 40, 41], extinction recall (the variable of interest for our aims) is operationalized as the change between the maximal startle response to the CS+ during acquisition in session 1 and the average startle response to the CS+ over the first block of extinction recall. Greater differences between CS+ responses during acquisition and extinction recall suggest stronger extinction recall [40].

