### Power considerations

No studies have examined the relationship between REM sleep and fear inhibition in an insomnia sample, nor have any attempted to reverse REM disruption to improve fear inhibition. Nonetheless, several studies from our team have demonstrated REM sleep-fear inhibition relationships in healthy controls and individuals with PTSD [19, 20, 24], with effect sizes ranging from *r* = 0.318 to *r* = 0.688 (medium to very large, per Cohen [73]), with a sample-size weighted average effect size of *r* = 0.477. Since that value is skewed towards healthy control studies, we will use an estimated effect size here of *r* = 0.40 (halfway between medium and large) for Aim 1 and a parallel effect size for Aim 2. Based on *r* = 0.40 and *α* = 0.05, *n* = 62 participants will provide power of 0.90 in Aim 1. For Aim 2, *f* = 0.33 (also medium-large) and *α* = 0.05, *n* = 66 provides power of >0.95 for Hypothesis 2a and >0.80 for the mediation analysis (Hypothesis 2b) [74].

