Hypothesis 2(b): Treatment effects on fear inhibition are driven by improvements in REM sleep specifically. To assess the degree to which treatment-related changes in fear inhibition are mediated by improvements in REM sleep, three separate bootstrap mediation analyses will be used. The first model will include the direct effect of treatment group (CBT-I vs. waitlist) on changes in fear inhibition, and changes in the REM Sleep latent variable (pre- to post-treatment) as a mediator variable. Identical models will then be employed to examine whether changes in slow wave sleep (N3%) or overall insomnia severity (ISI) are related to the changes in fear inhibition. This approach will allow us to assess whether treatment effects are mediated by changes specific to REM sleep, rather than general improvements in sleep. For the mediation analyses, bootstrapped confidence intervals will be used to test statistical significance of indirect effects. Mediation analyses will be carried out in Mplus [77], with statistical significance of indirect effect determined using 95% bootstrapped confidence intervals from 20 000 resamples. In an exploratory analysis, each of the three REM variables will also be examined separately as potential mediators.

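### Cue-set order, which the design counterbalances, is missing from the terms listed for the Aim 2 models; adding it is a small, nearly free gain in precision

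*Protocol article*

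**What the plan says.** All of this is in the protocol article.

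- **Task design** (Morning 1: fear/safety acquisition): to limit practice effects, "different visual cues will be used at each time point (pre- and post-treatment) and order will be counterbalanced". The text does not say whether the counterbalancing is done within treatment arm or only across the whole sample.
- **Allocation** (Randomization): "with a 1:1 allocation as per a computer-generated randomization schedule, stratified by sex (male vs. female), using permuted blocks". Cue order is not named as a factor.
- **Hypothesis 1** (Data analysis plan): "The analyses will include parameters for sex and serum estradiol as covariates".
- **Hypothesis 2a** (Data analysis plan): "The model will include parameters for treatment condition, baseline fear inhibition, sex, and serum estradiol as a covariate".
- **Hypothesis 2b** (Data analysis plan): "The first model will include the direct effect of treatment group (CBT-I vs. waitlist) on changes in fear inhibition", with change in the REM variable as mediator. No covariates are named.
- **Primary outcome** (Morning 3: extinction recall): "the change between the maximal startle response to the CS+ during acquisition in session 1 and the average startle response to the CS"+ in the first recall block. Within one time point the sessions use the same cues, and safety recall is likewise a within-cue change.

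Cue set and cue order appear in none of the listed models.

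**The concern.** Cue order is a factor that the design controls on purpose. Counterbalancing stops a cue-set difference from loading systematically onto one time point, but it does not take that difference out of the residual. Only a model term does.

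The crossover of cues makes this slightly worse than an ordinary omitted covariate. A participant whose baseline came from the cue set giving higher scores has a follow-up from the one giving lower scores, and the reverse holds in the other order. The cue effect therefore has opposite signs in the baseline covariate and in the outcome. Adjusting for baseline adds to the disturbance, and a change score carries it at full size.

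At stake is some precision in the primary treatment comparison and in the mediation model, with 66 completers expected.

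**Working it through.** **Inputs from the article.** Expected completers 66, taken as 33 per arm. For Aim 2, f = 0.33, which for two equal arms is d = 2f = 0.66. α = 0.05, taken as two-sided.

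**Assumptions.** The article gives neither a cue-set difference δ (in outcome SDs) nor a pre-post correlation ρ. I use δ = 0.2, 0.3, 0.5 and ρ = 0.5.

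**1. The plan's own figure.** The article states: "For Aim 2, *f* = 0.33 (also medium-large) and *α* = 0.05, *n* = 66 provides power of >0.95 for Hypothesis 2a". With a noncentral F, a 2 × 2 group-by-time interaction with λ = f²N·2/(1 − ρ) gives λ = 0.1089 × 66 × 2 = 14.37 and power 0.962 at ρ = 0, and more at higher ρ, so the figure reproduces in that form. The baseline-adjusted model listed for Hypothesis 2a has λ = f²N/(1 − ρ²) = 7.187/0.75 = 9.58 at ρ = 0.5, and power 0.86. That gap has nothing to do with cue order. It only means that the reference power below is about 0.86.

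**2. Residual variance.** Code the two orders as ±½, so the cue effect is −δ/2 or +δ/2 at baseline with the opposite sign at follow-up.

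- Baseline-adjusted: residual shift ±(δ/2)(1 + ρ), relative to variance 1 − ρ². Inflation = (δ²/4)(1 + ρ)²/(1 − ρ²) = (δ²/4) × 3 at ρ = 0.5.
- Change score: shift ±δ, relative to variance 2(1 − ρ). Inflation = δ²/[2(1 − ρ)] = δ² at ρ = 0.5.

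| δ | baseline-adjusted | change score |
|---|---|---|
| 0.2 | 0.0100 × 3 = 3% | 4% |
| 0.3 | 0.0225 × 3 = 7% | 9% |
| 0.5 | 0.0625 × 3 = 19% | 25% |

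Re-estimating the baseline slope with the cue effect present gives 3.0%, 6.6% and 17.6%, so the simple formula is adequate. Over ρ from 0.3 to 0.7 and the three values of δ, the ranges are 2–35% and 3–42%.

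**3. Hypothesis 2a power, order balanced overall but not within arm.** Simulation of the baseline-adjusted model, 33 per arm, d = 0.66, ρ = 0.5, 6,000 runs per cell:

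| δ | without term | with term | difference (points) |
|---|---|---|---|
| 0 | 0.852 | 0.844 | −0.8 |
| 0.2 | 0.851 | 0.852 | 0.2 |
| 0.3 | 0.836 | 0.850 | 1.4 |
| 0.5 | 0.800 | 0.856 | 5.7 |

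The mean estimate stayed at about 0.66 with and without the term. Type I error without the term was 0.048 to 0.054, which is 0.05 within simulation error (√(0.05 × 0.95/6000) = 0.003).

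**4. Hypothesis 2a power, order balanced within arm.** The estimate then keeps its small sampling error, but the model-based standard error is too large. Normal approximation at δ = 0.5:

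- True SE = √(0.75 × 2/33) = 0.213; model SE without the term = 0.213 × √1.176 = 0.231.
- With the term: Φ((0.66 − 2.0 × 0.213)/0.213) = Φ(1.10) = 0.86.
- Without it, balanced within arm: Φ((0.66 − 2.0 × 0.231)/0.213) = Φ(0.93) = 0.82.
- Without it, not balanced: Φ((0.66 − 2.0 × 0.231)/0.231) = Φ(0.86) = 0.80.

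The loss is about 4 points rather than 6. The matching simulation showed less (0.84 without, 0.85 with). However, 33 cannot be split evenly, and its 16/17 split always leaned the same way, which raised the mean estimate to 0.68 and flattered the model without the term. The test is conservative in this case: simulated type I error was 0.036 at δ = 0.5.

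**5. Chance imbalance is the same cost, not a second one.** With order balanced only overall, the between-arm difference in order share has SD 0.124. At δ = 0.5 the re-estimated slope is (0.5 − 0.0625)/1.0625 = 0.41, so the shift in the estimate has SD 0.124 × 0.5 × 1.41 = 0.087. Then √(0.213² + 0.087²) = 0.230, close to the simulated SD of 0.232. Imbalance is how the extra variance reaches the estimate.

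**6. Hypothesis 1.** Only one time point is used, so an unmodelled cue set adds variance δ²/4: 0.01, 0.0225 and 0.0625, that is 1%, 2% and 6% of the outcome variance.

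**The case against.** The case for leaving the plan alone is strong on several counts.

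- Counterbalancing is itself the design control. A covariate for it is optional and affects only precision. This stands, and it is why the point is minor.
- The article condenses a fuller document that may carry the term, and its wording does not say that the covariate list is complete. This stands in part. The article does list the model terms, and a factor that the design controls is not among them, so a one-line addition is a fair request.
- The cue-set difference is assumed. The examples are plain coloured circles, and both recall scores are differences within the same cue, so an additive effect of a cue set on startle drops out. Only a difference in conditioning or extinction between sets could matter. This stands in full: at δ = 0 there is nothing to gain.
- Up to 0.3 SD the power gain is 0 to 1 points. This stands too.

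A reader might infer that the cue swap biases the treatment comparison or leaves the arms unbalanced. The documents do not support that. Arm is randomised, so the expected bias is zero, and type I error is not inflated. Imbalance could arise only by chance, and only if order is not counterbalanced within arm, which the article states neither way. Nor should the variance figures be read as the same share of participants lost: 25% inflation leaves the equivalent of 66/1.25 = 52.8 participants, a loss of about 13, and only under the largest assumed difference in the change-score model.

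**Conclusion.** The point holds as a minor improvement in precision, not as an error or a source of bias. Cue-set order is absent from the listed Hypothesis 2a and 2b terms, and the opposite cue sets at baseline and follow-up mean that any difference in conditioning or extinction between sets goes into the residual with reinforced size. The practical cost is negligible up to a 0.3 SD difference. At 0.5 SD it becomes noticeable, whether as lost power or, with order balanced within arm, as a conservative test. These sizes rest on the assumed δ, ρ = 0.5, d = 0.66 and 33 completers per arm. The plan's stated power figure is not disturbed by this point.

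**What to change.** Add cue-set order (two levels) as a fixed effect in the Hypothesis 2a model and as a covariate in the Hypothesis 2b models, specified before outcome data are examined by arm. Optionally, add cue set as a covariate in the Hypothesis 1 regressions, and state that order is counterbalanced within arm, ideally within sex as well.

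The order must already be known for each participant in order to run the task, so no new data are needed. The cost is one degree of freedom, less than one power point if the cue sets turn out not to differ (0.852 against 0.844 in the simulation). Confirming within-arm counterbalancing costs a sentence, or a column in the allocation list if it is not yet done.
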